### **Secondary outcomes**

The first two secondary outcomes are binary at the level of prescription within patient. This will be aggregated to the patient level and logistic regression will be used to compare groups. HbA1C, blood pressure and LDL cholesterol are all continuous and measured at baseline and 9-12 months. An analysis of covariance (ANCOVA) model will be used (via linear regression) to provide the estimates of treatment effect adjusted for baseline values. Since these are all secondary analyses which are supportive or exploratory, no corrections for multiple testing will be applied and only patients with data will be included. However the ITT approach is

still followed as patients will remain allocated to their randomized groups irrespective of compliance.

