#### *2.6 What is the proposed duration of the treatment period?*

The treatment period will be for 24 months for each patient.

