#### *Secondary outcomes*

Adherence and appropriate prescribing will each also be secondary outcomes. For each, we will report the proportion of all prescriptions in each arm that meet the above criteria.

The mean change in HbA1c for patients with diabetes will be a secondary outcome. HbA1c levels will be mandatorily determined between 9 and 12 months and between 21 and 24 months after randomization in patients who had an HbA1c level measured no more than 6 months before randomization and who were prescribed a treatment for diabetes (e.g. metformin, gliclazide, or insulin). HbA1c is easy to assess, is routinely measured and is known to be associated with clinically important outcomes such as myocardial infarction and mortality[42].

The mean change in blood pressure for patients with hypertension or diabetes will be a secondary outcome. This will be assessed mandatorily between 9 and 12 months and between 21 and 24 months after randomization in patients who had a blood pressure reading recorded no more than 6 months before randomization and who are prescribed an antihypertensive treatment. Blood pressure is routinely measured and is known to be associated with clinically important outcomes such as myocardial infarction,[43] stroke[44] and mortality.[45]

The mean change in low density lipoprotein cholesterol (LDL) will be a secondary outcome. LDL will be determined mandatorily between 9 and 12 months and between 21 and 24 months after randomization in patients who had an LDL level measured within 12 months of randomization and who are prescribed a statin. LDL levels are routinely measured and known to be associated with clinically important outcomes such as myocardial infarction, stroke and mortality [46]. Reductions in LDL by statins and other treatments reduce the risk of death based on multiple statin trials and preliminary results from the IMPROVE-IT trial (ezetimibe-simvastatin versus statin) presented in November of 2014 [47].

HbA1c, blood pressure and LDL will be assessed by audits of the EMR.

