### **Treatment and follow up period**

The treatment period will be for 24 months for participants in the control arm and 36 months for participants in the intervention arm.

For the primary analysis, the follow up period is 24 months for all participants. Medication adherence and health outcomes data (blood pressure, HbA1c levels and cholesterol levels) will be collected during regularly scheduled appointments. Inappropriate prescribing, prescription records and costs will be reviewed from the electronic medical records. The total follow up period is identical to the treatment period.

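### The current SAP and protocol section 2.16 still place HbA1c, blood pressure and LDL at baseline and 9–12 months, so the mandatory 21–24 month values have no stated analysis

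*Supplement*

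**What the plan says.** **Measurement (latest protocol).** Section 2.6 sets the length of treatment: "The treatment period will be for 24 months for each patient". Section 2.7 gives follow-up the same length. Section 2.9 then fixes when the clinical outcomes are taken:

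- HbA1c: "HbA1c levels will be mandatorily determined between 9 and 12 months and between 21 and 24 months after randomization"
- Blood pressure: "This will be assessed mandatorily between 9 and 12 months and between 21 and 24 months after randomization"
- LDL: "LDL will be determined mandatorily between 9 and 12 months and between 21 and 24 months after randomization"

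Each applies to patients with a sufficiently recent pre-randomization value and a relevant prescription. The values are collected by audit of the medical record.

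**Analysis (SAP of 9 September 2019).** Under Treatment and follow up period: "For the primary analysis, the follow up period is 24 months for all participants". The outcome list gives the three clinical outcomes as baseline-adjusted and names no visit. Under Secondary outcomes the SAP says that "HbA1C, blood pressure and LDL cholesterol are all continuous and measured at baseline and 9-12 months", and continues: "An analysis of covariance (ANCOVA) model will be used (via linear regression) to provide the estimates of treatment effect adjusted for baseline values". Only patients with data are included, and there is no multiplicity correction. Section 2.16 of the latest protocol repeats these sentences.

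**Treatment length.** The SAP also states: "The treatment period will be for 24 months for participants in the control arm and 36 months for participants in the intervention arm". It equates total follow-up with the treatment period.

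**The concern.** The sentence on measurement times is word for word the one in the SAP of 20 April 2016, when follow-up was 12 months and 9–12 months was the only post-baseline window. The trial was extended and a second mandatory window was added, but the sentence was not changed. The current measurement plan and both current analysis sections therefore disagree.

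There are two ways this can go wrong:

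- If the analysis text is followed, adherence over 24 months is set beside clinical measures from the first year, and the second-year clinical values are collected but not used.
- If it is not followed, someone must choose between 9–12 months, 21–24 months or some combination, for three outcomes, with no rule to guide the choice. The documents do not show whether that choice would come before sight of the data.

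**Working it through.** The plan gives no numerical figure on this point, so the check is mainly a comparison of passages.

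**1. Windows mandated against windows named in the analysis**

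| Outcome | Mandatory follow-up (protocol 2.9) | Named in analysis text (SAP; protocol 2.16) |
|---|---|---|
| HbA1c | 9–12 and 21–24 months | 9–12 months |
| Blood pressure | 9–12 and 21–24 months | 9–12 months |
| LDL | 9–12 and 21–24 months | 9–12 months |

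Mandated: 3 outcomes × 2 windows = 6. Named: 3 × 1 = 3. Without a stated analysis: 6 − 3 = 3, namely the 21–24 month window of every clinical outcome.

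**2. Does any other place supply the missing analysis?**

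- The outcome lists (protocol 2.8 and SAP Outcomes) name no visit.
- Protocol 2.17 says only that analysis follows completion of the study.
- Protocol 2.18 covers age and sex subgroups and names no visit.
- The summary of changes mentions the extension but not the clinical outcomes.
- No section gives a repeated-measures model, a pooling rule or a choice between the two windows.

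**3. Is the primary design affected?** The one computed design figure is 392 per group. With pooled variance, two-sided alpha 0.05 (z = 1.960), power 0.80 (z = 0.842) and difference d = 0.10,

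n = [1.960·√(2·p̄·(1−p̄)) + 0.842·√(p₁(1−p₁) + p₂(1−p₂))]² / d².

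For 45% v 55%: [1.960·√0.500 + 0.842·√0.495]² / 0.01 = (1.386 + 0.592)² / 0.01 ≈ 391.3, which rounds up to 392. Other control rates give 388 (40%), 388 (50%), 376 (55%) and 356 (60%). So 392 reproduces as the worst case over the stated range. It concerns appropriate adherence only and does not depend on the visit used for the clinical outcomes.

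**4. Can a power loss be computed for the clinical outcomes?** No. The documents give no standard deviation, target difference, subgroup size or between-visit correlation for HbA1c, blood pressure or LDL.

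**5. Treatment and follow-up length**

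- Protocol 2.6 and 2.7: 24 months for every patient.
- SAP: 24 months (control) and 36 months (intervention), with 24 months fixed explicitly for the primary analysis.
- Protocol 2.9: healthcare use and costs ascertained for 2 years after randomization, with no difference by arm.

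The first two conflict. The third already gives an equal window for one secondary outcome, but the SAP states none for the others.

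**The case against.** The strongest reply is that neither analysis section says the later values are excluded. The disputed sentence describes measurement times, the ANCOVA sentence names no visit, and protocol 2.9 sets out both windows. An ANCOVA at each visit would be compatible with all of this. The SAP also ties its 24-month statement to the primary analysis, so a first-year clinical analysis may have been intended. Finally, these outcomes are labelled supportive or exploratory.

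Part of this stands. A reader might infer that the plan restricts the clinical analysis to 9–12 months and rules out a two-year estimate. The text does not go that far: it names one window and is silent on the other. The exploratory label also stands and lowers the severity.

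The rest does not remove the point. As a description of the data, the sentence conflicts with protocol 2.9. No passage says a first-year analysis was intended, and protocol 2.7 justifies 24 months partly by the evaluation of clinical outcomes. On either reading the 21–24 month values have no stated analysis.

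Two further inferences are tempting but not supported:

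- **A large gain in precision from using both visits.** Such a gain would apply to the effect averaged over the two visits, and its size rests on correlations the documents do not give. For the 21–24 month contrast with complete data, a repeated-measures model with unstructured covariance and visit-specific baseline effects gives essentially the same answer as ANCOVA at that visit. The gain there comes only from patients with one follow-up value missing.
- **Cumulative outcomes counted for longer in the intervention arm.** No passage takes any outcome over total follow-up, and protocol 2.9 fixes healthcare use and costs at 2 years. What remains is that the SAP does not state the window for the other secondary comparisons.

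**Conclusion.** Wrong as written, and it should be fixed. The current SAP and protocol 2.16 misstate when HbA1c, blood pressure and LDL are measured, and they leave the 21–24 month values of all three without a stated analysis. These are three of six secondary outcomes, and the trial's only clinical ones. The primary outcome, its test, its 24-month window and its sample size are unaffected, so this is not a fault that must be cured before the trial can answer its main question.

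The conclusion assumes that the windows in section 2.9 of the latest protocol are the current measurement plan. It needs no assumption about effect sizes or correlations. The disagreement over treatment and follow-up length is a separate inconsistency and does not raise the severity of this point.

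**What to change.** 1. In the SAP (Secondary outcomes) and protocol 2.16, give the measurement times as baseline, 9–12 months and 21–24 months.
2. Estimate the baseline-adjusted treatment effect at each follow-up visit. Name 21–24 months as the main secondary time point, to match the primary analysis, and report 9–12 months beside it.
3. Preferably use a repeated-measures linear model with a treatment-by-visit term, which also uses patients who have only one of the two follow-up values. A separate ANCOVA at each visit is an acceptable simpler form.
4. Separately, reconcile the treatment and follow-up lengths in protocol 2.6 and 2.7 with those in the SAP. State that secondary comparisons between arms use the 24-month window, as protocol 2.9 already does for healthcare costs.

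The cost is a few sentences in two documents and, for the repeated-measures form, a slightly more complex model. No new data are needed, because both measurements are already mandatory.

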### **Summary of changes to CLEAN Meds trial protocol**

The duration of the trial was extended from 12 months to 24 months when additional funding was secured.

For the analysis of the primary outcome, we originally planned to use electronic pill bottle cap devices in one-seventh of participants to confirm adherence measurements but due to a large amount of missing data in both arms after 12 months, we stopped using the electronic pill bottle cap devices.

We added details about the healthcare cost data collection.
